#### Economic Evaluation

The economic evaluation will be designed to identify the costs associated with implementation, and the net costs to health care funders. Costs of the OptimalMe implementation package will be identified from the trial data, including the costs of platform maintenance, staff time (in providing the coaching sessions), and SMS text messages. Fixed and variable costs will be identified, allowing cost per woman to be estimated at different scales of the intervention. The net costs to health care funders will be identified by quantifying the costs associated with birth type, birth complications, neonatal intensive care unit admissions, hospital stay, and ancillary utilization. Costs to Medicare Benefits Schedule will be identified based upon item numbers [51] associated with birth type and complications. Costs to private health insurers associated with hospital stay will be identified directly from the study. Costs to public hospital funders from neonatal intensive care unit admissions or any public hospital transfers will be identified from the National Hospital Cost Data Collection produced by the Independent Hospital Pricing Authority [52]. The total cost per woman will be calculated, and generalized linear models will be utilized to identify differences in costs between delivery methods. We will use these models to estimate the net cost impacts to different funders at different levels of the population reached.

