### Specific Objectives

Our objectives are as follows:

Determine implementation feasibility with 1) process evaluation (ie, measure of process used to implement the program and any variation experienced; facilitators and barriers to intervening events impacting implementation), 2) the RE-AIM framework to assess Reach, Effectiveness, Adoption, Implementation and Maintenance of the intervention and 3) cost effectiveness analysis.Evaluate intervention participation (ie, engagement and adherence to program) and engagement (ie, degree of online module completion, frequency, and duration of time spent on the platform).Determine intervention effectiveness on health related outcomes measured at the individual level including health knowledge, health literacy, and self-management behaviors.Determine any discrepancy according to the health coaching delivery method.

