### Hypotheses

We hypothesize as follows:

The intervention will be feasible to implement and can effectively reach and engage women prior to pregnancy through co-designed strategies that are acceptable to women and the implementation partner with demonstrated cost-effectiveness.Participation and engagement with intervention resources will be greater for participants who complete the intended intervention dose compared with those who do not.The intervention will improve preconception and pregnancy health knowledge and self-management.Phone and videoconference health coaching delivery will be equally feasible and cost-effective, yet engagement, adherence, and effectiveness will be greater with videoconference compared with phone-based health coaching.

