## Methods

### Implementation

#### Design

OptimalMe is a type 3 hybrid effectiveness-implementation study [35] with an active intervention phase (2 years) and a passive observation phase (up to 5 years). Type 3 hybrid implementation designs are those in which implementation outcomes are primary, and individual or population outcomes are secondary [35]. The primary outcome of the project includes overall intervention penetration and reach and the feasibility, acceptability, adoption, and fidelity of the delivery of OptimalMe. Secondary outcomes include evaluation of individual health outcomes associated with implementation delivery mode, including knowledge, risk perception, health literacy, self-management, and health behaviors. The study design is a parallel, two-arm, randomized trial at the level of the individual utilizing a pragmatic philosophy, working within real-world conditions to assess overall effectiveness. All individuals will receive the same evidence-based lifestyle intervention, and implementation delivery methods will be compared.

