### Outcome Measures

Outcome measures (Table 1) are underpinned by the RE-AIM (Reach, Effectiveness, Adoption, Implementation and Maintenance [45]). Both quantitative (recruitment and intervention delivery fidelity checklists [46]) and qualitative (semistructured interviews) data collection methods will be used (Multimedia Appendix 1 and Multimedia Appendix 2).

**Table 1 table1:** Description of outcome measures.

Outcome			Description
**Implementation feasibility (primary)**			Program evaluation and feasibility for future scale up
	Reach	Proportion of the target population that were invited and participated in the program and intervening factors	
	Implementation fidelity	Delivery according to design and any variation experienced Facilitators and barriers: identification and description of intervening events	
	Adoption of the program by the implementation partner	Contextual events or factors influencing implementation within the setting, variation in any co-design implementation component	
	Cost-effectiveness	To answer questions about overall feasibility of implementation	
**Intervention effectiveness (secondary)**			Exploratory evaluation of the effectiveness of intervention delivery across preconception and pregnancy (Figure 1)
	Participation	Adherence and engagement measures to intervention dose including health coaching sessions and web-based platform interaction including degree of module completion, frequency and duration of time spent on the platform	
	Acceptability	A set of questions relating to the influence of the program in changing health behaviors, the usefulness and relevancy of the information provided, valuable aspects of the program and areas for improvement Qualitative data analysis of insights, participation factors, intervention reach, adoption and maintenance of behavior change, intervention delivery format, and areas for improvement until thematic data saturation	
	Effectiveness	On individual health behaviors including self-reported weight, health literacy [47], self-management [48], diet [49], and physical activity [50] using validated questionnaires Collected at the start of the intervention, after preconception health coaching sessions and module, and at the start of the pregnancy module	

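### The plan promises programme cost-effectiveness and net cost impact by reach, but it costs only OptimalMe recipients and contrasts only telephone with videoconference, so neither can be estimated

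*Protocol article*

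**What the plan says.** **What is promised.** Under Specific Objectives, the first objective includes a "cost effectiveness analysis". Under Hypotheses, the first expects strategies that are "acceptable to women and the implementation partner with demonstrated cost-effectiveness". The fourth expects that "Phone and videoconference health coaching delivery will be equally feasible and cost-effective", with greater engagement, adherence and effectiveness by videoconference. Table 1 places a cost-effectiveness row under "Implementation feasibility (primary)" and describes it only as "To answer questions about overall feasibility of implementation".

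**How the narrative defines the primary outcome.** The Design section under Implementation states: "The primary outcome of the project includes overall intervention penetration and reach and the feasibility, acceptability, adoption, and fidelity of the delivery of OptimalMe". Cost-effectiveness is not in that list, nor in the lists in the abstract and under Framework.

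**What is planned.** The Economic Evaluation section covers programme costs (platform, staff time, text messages), cost per woman at different scales, and the costs of birth and related care to each funder: "The net costs to health care funders will be identified by quantifying the costs associated with birth type, birth complications" and further items. A total cost per woman is then calculated. Generalized linear models compare costs between delivery methods, and the same models are to give net cost impacts for different funders at different levels of reach.

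**What the design compares.** "All individuals will receive the same evidence-based lifestyle intervention"; only the coaching mode differs.

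**The concern.** A cost-effectiveness claim needs two differences against a stated alternative, one in cost and one in effect. For hypothesis 1 the alternative is not having OptimalMe. The economic plan names no effect to set against cost, and the design holds no women without the programme.

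The word net raises the same difficulty. A net cost is a difference from what would have been spent otherwise. Adding up what was spent on births among participants gives a total, whatever it is called.

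What is at stake is the scale-up advice. The net impact by reach is the figure a health care funder would use to decide whether to extend the programme, and the implementation partner, which also funds the project, is an insurer. If it is reported as planned, readers may take it as evidence that OptimalMe saves or costs a given amount when the trial holds no information on that.

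**Working it through.** No stated figure has to be reproduced, so the check asks which quantities the design can supply.

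**Notation.** C and E are mean cost and mean effect per woman; T and V are the telephone and videoconference arms; 0 is the absence of OptimalMe; N is the eligible population and r the proportion reached.

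| Quantity | Source in the plan | Available? |
|---|---|---|
| C_T, C_V | Economic Evaluation: total cost per woman, modelled by delivery method | Yes, randomised |
| E_T, E_V | Table 1: participation, health literacy, self-management, diet, physical activity, weight | Yes, randomised |
| C_0 | No untreated arm; no historical or external group named | No |
| E_0 | As for C_0; Statistical Analysis offers before-after regressions | Not as a concurrent comparison |

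**Step 1. Hypothesis 1, programme cost-effectiveness.** Write C_1 and E_1 for the mean cost and effect among OptimalMe recipients. The claim needs C_1 − C_0 and E_1 − E_0. C_0 is unobserved. A before-after contrast cannot stand in for it, because delivery type, birth complications and neonatal intensive care admission have no baseline value in the same pregnancy.

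**Step 2. Net cost impact by reach.** Raising reach moves women from no programme to programme, so the impact is N × r × (C_1 − C_0). The planned models estimate C_V − C_T. C_0 does not appear in that difference: any value of C_0, above or below C_1, fits the trial data equally well. The sign of the net impact is therefore undetermined. What can be scaled is the cost of delivering the programme, for which the plan already separates fixed from variable costs.

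**Step 3. Hypothesis 4, telephone versus videoconference.** The claim needs C_V − C_T and E_V − E_T. All four terms are collected in randomised arms, so relative cost-effectiveness can be estimated. The Economic Evaluation section uses only the first difference and does not link it to the second.

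**Step 4. Status of the outcome.** Table 1 puts cost-effectiveness under the primary heading; the three narrative lists leave it out. Its primary status rests on Table 1 alone. Objective 1 and hypothesis 1 make the promise regardless.

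**The case against.** The strongest defence is condensation. The economic section is one paragraph of a journal article, and the choice of effect unit, ratio and method for uncertainty is commonly left to a fuller economic plan. That stands for the between-mode comparison: a fuller plan could supply the missing link, and its absence here is a modest gap. It does not rescue hypothesis 1 or the reach extrapolation. Those lack a comparison group in the design as described, and specifying the analysis of these participants in more detail cannot create one.

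A second defence is that net means only the difference between modes, since the net impacts are to come from the models of that difference. On that reading, birth costs common to both arms cancel and the figure is legitimate. But it then says nothing about the effect of reaching more women, which is the use the plan gives it.

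Three stronger readings are tempting, and the documents do not support them:

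- A reader might infer that no cost-effectiveness result of any kind is possible. The randomised arms and the effects in Table 1 contradict this for hypothesis 4.
- A reader might infer that cost-effectiveness is plainly a primary outcome throughout. The narrative definitions omit it.
- A reader might infer that the net cost per woman will be wrong by about a whole delivery cost. The article never defines net as programme cost plus birth cost, and it openly calls the per-woman sum a total. The fair criticism is that net is undefined and, for the programme, has nothing to be net of.

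**Conclusion.** The point holds at the level of the programme. Objective 1, hypothesis 1 and Table 1 promise cost-effectiveness, while the economic plan holds costs and one contrast, between coaching modes. With 0 of about 300 women observed without OptimalMe and no external group named, programme cost-effectiveness and net impact by reach cannot be estimated. For hypothesis 4 the comparison can be made but is not planned: only costs are compared.

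No monetary size can be given, because the documents contain no unit costs and no definition of net. The conclusion assumes that no outside comparator exists in a document not shown; the article mentions none.

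This should be fixed, but it does not threaten the trial. Randomisation, data collection and the other outcomes are unaffected.

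**What to change.** **(a) Match the claims to the design.**
- Remove demonstrated cost-effectiveness from hypothesis 1.
- Relabel the item in objective 1 and Table 1 as implementation cost plus a between-mode cost-effectiveness or cost-consequence analysis, and state consistently whether it is primary.
- Describe birth-related costs as total costs by funder, and keep the word net for the difference between modes.
- Present the reach extrapolation as programme delivery cost by scale, not as net impact.

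**(b) Complete the comparison for hypothesis 4.** Name one effect already collected in both arms, for example completion of the coaching sessions due. Report incremental cost and incremental effect, each with an interval, over all randomised women.

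**An outside comparison is exploratory at most.** Because invitees are randomly selected, one could compare members by invitation status in the insurer's data. Opt-in uptake would dilute it heavily. At about 500 invitations a month, and assuming 12 months of recruitment (the duration is not stated), 12 × 500 = 6000 invitations yield 300 participants, or 5%, a dilution of 1/0.05 = 20-fold. Over 24 months it is 300/12,000 = 2.5%, or 40-fold. The uninvited pool is also small: 7800/12 = 650 joiners or upgraders a month less 500 gives about 150, and some of these could be invited later because eligibility spans 3 months. This route should not carry a main claim.

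**Cost.** (a) is wording. (b) is one modest additional analysis of data already planned for collection. The drawback is a less favourable headline claim.

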### Ethical Approval

The Monash Health Human Research and Ethics Committee approved the study (RES-19-0000291A), and the study has been registered (using predefined study description classifications; as such, the trial was registered as an efficacy trial in the absence of a feasibility study descriptor) on the Australian and New Zealand Clinical Trial Registry (ACTRN12620001053910).

## Results

The project is supported with funding from Medibank Private Ltd. Recruitment commenced in July 2020 with results expected to be published in 2022.

## Discussion

Prevention of weight gain and obesity is a global health priority. Increased emphasis is placed on high-risk populations [53,54], including reproductive-age women with accelerated preconception, pregnancy, and postpartum weight gain [6]. Lifestyle interventions can be used to optimize weight and reduce maternal and neonatal adverse outcomes [12,55], yet translation of effective interventions into real-world settings remains critically limited. We address this gap and leverage extensive investments in efficacy research by undertaking implementation research to inform feasibility, acceptability, applicability, effectiveness, and sustainability of an evidence-based weight gain prevention intervention for preconception, pregnancy, and postpartum periods. Implementation research leverages investment in efficacy-based randomized trial knowledge to study methods that promote the systematic uptake of evidence-based interventions into practice and policy to improve health [35].

Our study design aligns with best practice implementation research; focuses on system-level outcomes; and is underpinned by evidence from efficacy trials, systematic reviews, meta-analyses, and guidelines. Additional health information, specific to preconception, pregnancy, and postpartum life stages, has been integrated, with checklists and resources. Evidence on core and peripheral components has been integrated to adapt the intervention with stakeholders across women, multidisciplinary clinicians, and partners. Novel delivery strategies, including sophisticated digital platform and remote health coaching delivery methods, while retaining core intervention features including low-intensity individual health coaching and ongoing text message support. This work has integrated, and been supported by, robust implementation and intervention frameworks and theories.

We anticipate that the OptimalMe intervention will demonstrate feasibility and directly provide evidence to inform scaled intervention delivery. Learning will not only inform future implementation design but translation of evidence targeting consumers, program facilitators, health professionals, services, and policy makers to inform future scale up of healthy lifestyle interventions to ultimately benefit the health of women.

## Appendix

Multimedia Appendix 1 Co-designed recruitment strategy.

Multimedia Appendix 2 OptimalMe health-related content (fact sheets) within preconception, pregnancy, and postpartum modules.

Multimedia Appendix 3 CONSORT eHEALTH Checklist (V 1.6.1).

## Abbreviations

BMI: body mass index
